**9.5.1 Primary Outcome**

Primary outcome for the study is incidence of preterm birth and low birth weight. It will be measured by the outcome assessors at the time of follow up visit after delivery.

**9.5.2 Secondary Outcomes**

Secondary outcome is incidence of other maternal and perinatal morbidities and it will be measured during the same visit as the primary outcome.

**9.6 Data Analyses**

Pearson’s chi square will be used for analyzing data, after tabulation of categorical dichotomous variables in a 2x2 table, drawn between the outcome of preterm birth or low birth weight, and arm in which the incidence occurred.

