**1.2 Secondary Objectives**

The secondary objective will be to measure other maternal and perinatal complications occurring in the enrolled pregnant women so as to look for confounders if any.

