**2. BACKGROUND AND RATIONALE**

**2.1 Background on Condition, Disease, or Other Primary Study Focus**

Urinary tract infection includes asymptomatic subclinical infection and symptomatic disease. It may involve any part of urinary tract like urethra, bladder, ureter, kidneys.

**Asymptomatic bacteriuria** in women is the presence of more than 100000 colony forming units of same bacterial strain in each mL of two consecutive urine samples collected by voided midstream clean-catch or at least 100 colony forming units per mL of catheterized specimen, in the absence of any symptoms of urinary tract infection (UTI) [1]. It is mostly caused by Escherichia coli, but Klebsiella pneumoniae, coagulase-negative Staphylococci, Enterococcus species, group B streptococci, and Gardnerella vaginalis are also reported in few cases [1].

**Uncomplicated urinary tract infection** in nonpregnant outpatient women without anatomic abnormalities or instrumentation of the urinary tract when involves lower urinary tract, it is called cystitis, while if it involves upper urinary tract, it is called pyelonephritis. The signs and symptoms of cystitis are- urinary frequency, urgency, dysuria, nocturia, supra-pubic discomfort, low-back pain, haematuria. The signs and symptoms of pyelonephritis are- flank pain, nausea, vomiting, fever (>38ºC), costo-vertebral angle tenderness, chills. Complicated urinary tract infection encompasses all other types of UTI.

Asymptomatic bacteriuria in pregnancy if untreated, may progress to cystitis or pyelonephritis, and may lead to adverse outcomes like preterm labour, hypertensive disease and preeclamptic toxemia, anaemia or post-partum endometritis [2, 3]. Acute pyelonephritis can also lead to transient renal failure, Acute Respiratory Distress Syndrome, sepsis, shock and haematological abnormalities [4]. In baby, it can lead to urinary tract infections in baby, low birth weight, intrauterine growth retardation, and higher perinatal mortality rate [2, 3, 5].

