**9. STATISTICAL CONSIDERATIONS**

**9.1 General Design Issues**

The process of development of prematurity and low birth weight due to asymptomatic bacteriuria is largely insidious and multifactorial. Training status of lab technicians, resource availability, adherence to guidelines, myths among the providers regarding asymptomatic nature of the disease and lack of habit of conducting point-of-care tests in routine antenatal check-ups introduce variability at facility level. Hence, to study the effect of early diagnosis of asymptomatic bacteriuria and subsequent targeted therapy in real-world situation, pragmatic randomized controlled trial design was chosen. The primary hypothesis is that early diagnosis and treatment of asymptomatic bacteriuria will decrease preterm and low birth weight. The primary outcome measure is incidence of preterm and/or low birth weight in usual care of a setting and in an intervention arm with early diagnosis using rapid test and subsequent informed treatment with antibiotics. Hence parallel study design was chosen to prove the superiority of the intervention. Secondary hypothesis was that some co-morbidities can be confounders for preterm and low birth weight which are otherwise multifactorial. Hence, secondary outcome measure was the incidence of maternal and perinatal co-morbidities.

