**9.2 Sample Size and Randomization**

Sample size was calculated based on type 1 error of 5%, power of 80%, global rate of preterm birth as 10.6% and that of low-birth-weight as 14.6%, combined rate of preterm or low-birth-weight (primary outcome measure) extrapolated as 25%. Based on the contribution of asymptomatic bacteriuria to total preterm birth and low-birth-weight, which varies from 6.9% to 20.5%24, the expected incidence of preterm birth or low-birth-weight in intervention arm for sample size calculation, was safely assumed to be 15% lower than the above-extrapolated global incidence of 25% in the control arm, as a minimally important difference for success of the experiment. Loss to follow up was accounted for 10% participants (5% in each arm). The sample size calculation estimated 120 participants to be enrolled in each arm, with a total 240 participants to be enrolled in the study.

Intention-to-treat analysis will be done in the original groups in which the participants are allocated. Incidence of other maternal and perinatal events will be described as frequencies. In case there is loss to follow up, complete case analysis will be done. In case there is any protocol deviation, per protocol analysis will be done.

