**15. SUPPLEMENTS/APPENDICES**

**Appendix 3 Data Collection Format for Study Enrollment and Record of Laboratory Reports**

| **RECORD OF ENROLLED MOTHERS** | | | | |
| --- | --- | --- | --- | --- |
| **DATE OF EVALUATION-** | |  | **OPD REGISTRATION NUMBER-** | |
| **ANC NUMBER-** | |  | **LAB NUMBER-** | |
|  | |  |  | |
| **A. Identification Data** | |  | **D. Enrolment details** | |
| **Name-** | |  | **Arm** **of** **the** **study** **for** **which** **woman** **is** **enrolled** | ❑ **Asymptomatic** |
| **Husband’s** **name-** | |  |  | ❑ **Symptomatic** |
| **Address-** | |  | **ENROLMENT NUMBER-** | |
|  |  |  |  | |
| **Mobile/phone** **number-** | |  | **E. Demographic and socioeconomic profile** | |
| **Alternate** **number** **if** **available-** | |  | **Age-** | |
|  | |  | **Religion-** | |
| **B. Exclusion Criteria** | |  | **Education-** | |
| **Has** **pregnant** **woman** **received** **any** **antibiotics** **in** **last** **two** **weeks?** | ❑ **Yes** |  |  | |
|  | ❑ **No** |  | **F. Antenatal data** | |
|  | |  | **No** **of** **previous** **ANC** **visits-** | |
| **Is** **woman** **pregnant** **for** **more** **than** **38** **weeks?** | ❑ **Yes** |  | **Gestational** **age** **in** **weeks-** | |
|  | ❑ **No** |  | **Number** **of** **previous** **pregnancies-** | |
|  | |  | **Number** **of** **abortions-** | |
| **Was** **she** **tested** **for** **Rapid** **Strip** **test** **in** **any** **arm** **of** **study** **earlier?** | ❑ **Yes** |  | **Number** **of** **live** **children-** | |
|  | ❑ **No** |  |  | |
|  | |  | **Was** **she** **tested** **or** **treated** **for** **UTI** **earlier** **in** **this** **pregnancy?** | ❑ **Yes** |
|  | |  |  | ❑ **No** |
| ***Enrolled in the study?*** | ❑ **Yes** |  |  | |
|  | ❑ **No** |  | **G. Study Seal** | |
|  | |  |  | |
| **C. Symptoms- (Tick whichever are applicable-one or**  **more)** | |  |  |  |
| ***Cystitis*** | |  |  |  |
| **Going** **for** **passing** **urine** **frequently** | ❑ |  |  |  |
| **Feel** **like** **urgently** **passing** **urine** | ❑ |  |  |  |
| **Pain/burning** **sensation** **during** **passing** **urine** | ❑ |  |  |  |
| **Urge** **to** **pass** **urine** **at** **night** | ❑ |  |  |  |
| **Lower** **abdominal** **pain** | ❑ |  |  |  |
| **Low-back** **pain** | ❑ |  |  |  |
| **Bleeding** **in** **urine** | ❑ |  |  |  |
| ***Pyelonephritis*** | |  |  |  |
| **Pain** **on** **the** **side** **of** **the** **abdomen** | ❑ |  |  |  |

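### The primary test leaves out gestational age at entry, which is already recorded, and the secondary objective and hypothesis call later complications confounders

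*Protocol*

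**What the plan says.** **Primary analysis.** Section 9.6 states that Pearson's "chi square will be used for analyzing data, after tabulation of categorical dichotomous variables in a 2x2 table", crossing study arm with preterm birth or low birth weight. It names no covariate and no other primary analysis.

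**Design around it.** Section 4.1 admits women in any trimester at their first antenatal check-up. Section 3 uses simple randomisation with no restriction, so the design does not balance gestational age between arms. Appendix 3 records gestational age in weeks at enrolment under "F. Antenatal data", together with the number of previous pregnancies; age is in its demographic block.

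**Complications.** Section 1.2 sets the secondary objective as "to measure other maternal and perinatal complications occurring in the enrolled pregnant women so as to look for confounders if any". Section 9.1 repeats the idea: "Secondary hypothesis was that some co-morbidities can be confounders for preterm and low birth weight which are otherwise multifactorial". Section 9.5.2 measures these morbidities at the same post-delivery visit as the primary outcome. For their analysis, section 9.2 plans only a description by frequency.

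**Causal account.** Section 2.1 says that untreated asymptomatic bacteriuria "may progress to cystitis or pyelonephritis, and may lead to adverse outcomes like preterm labour, hypertensive disease and preeclamptic toxemia".

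**The concern.** There are two separate faults.

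First, the one prespecified test leaves out a baseline variable that the trial already collects. Gestational age at entry is likely to matter for preterm birth almost by construction: a woman who enrols late has already passed through part of the period in which she could deliver preterm, and treatment has less time to act. With unrestricted allocation, the arms may differ on it by chance, and the planned test takes no account of this.

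Second, the protocol looks for confounders in the wrong place. A confounder of a randomised comparison would have to precede allocation. Complications that develop afterwards cannot play that role, and on the protocol's own account some of them lie on the path from untreated bacteriuria to early delivery. An analyst who followed the stated purpose and adjusted for them, or stratified on them, could remove part of the effect the trial is meant to detect or introduce bias.

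**Working it through.** **1. Reproduce the planned sample size.** Inputs from section 9.2: "type 1 error of 5%, power of 80" per cent; "combined rate of preterm or low-birth-weight (primary outcome measure) extrapolated as 25" per cent in the control arm; the intervention arm "safely assumed to be 15% lower than the above-extrapolated global incidence of 25% in the control arm"; 5% loss per arm; 120 per arm stated. Reading the effect as 15 points absolute (25% v 10%) and the test as two-sided:

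- Mean risk = 0.175. n = [1.96 × √(2 × 0.175 × 0.825) + 0.8416 × √(0.25 × 0.75 + 0.10 × 0.90)]² / 0.15² = 99.5, so 100 per arm.
- With continuity correction: 113 per arm.
- With 5% loss: 113 / 0.95 = 119, which agrees with 120.

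The relative reading (25% v 21.25%) needs 1,984 per arm before loss, so it is not what produced 120.

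**2. Power of the unadjusted test.** Evaluable per arm = 120 × 0.95 = 114. Power = Φ{[0.15 × √114 − 1.96 × √(2 × 0.175 × 0.825)] / √0.2775} = Φ(1.04) = 85.1%.

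**3. Gain from adjusting.** If gestational age at entry explains a share R² of outcome variance, the variance of the estimated difference is multiplied by (1 − R²), so the effective size is 114 / (1 − R²). R² is not in the protocol; the values below are assumed.

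| Assumed R² | Effective n per arm | Fall in standard error | Power |
| --- | --- | --- | --- |
| 0 | 114.0 | – | 85.1% |
| 0.01 | 115.2 | 0.5% | 85.5% |
| 0.02 | 116.3 | 1.0% | 85.8% |
| 0.05 | 120.0 | 2.5% | 86.9% |
| 0.10 | 126.7 | 5.1% | 88.6% |
| 0.20 | 142.5 | 10.6% | 91.9% |

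**4. Check by simulation.** 3,000 runs per setting, 114 per arm, assumed entry mix 40/40/20% by trimester, 25% v 10%. The chi-square was compared with a trimester-adjusted risk difference using robust standard errors. Monte Carlo error is about 0.6 points.

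| Assumed odds ratio per later trimester | Chi-square | Adjusted |
| --- | --- | --- |
| 1 | 85.9% | 85.8% |
| 0.67 | 86.5% | 86.0% |
| 0.5 | 85.5% | 86.4% |
| 0.33 | 86.6% | 88.4% |

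A gain clear of simulation error appears only when gestation is strongly prognostic.

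**5. Chance imbalance.** For a third-trimester share p, the standard deviation of the arm difference at 120 per arm is √(2p(1 − p)/120). For assumed p = 0.2, 0.3 and 0.4 this is 0.052, 0.059 and 0.063, so the probability of a difference above 10 points is 5.3%, 9.1% and 11.4%. If late entrants' risk differs by an assumed 13 points, a 10-point imbalance moves the crude difference by 0.10 × 0.13 = 1.3 points. The standard error of that difference is √(0.2775/114) = 4.9 points, so the shift is about a quarter of one standard error. These same assumptions imply a small R²: p(1 − p) × 0.13² runs from 0.0027 to 0.0041, against an outcome variance of 0.144 (mean risk 0.175) to 0.188 (risk 0.25). That gives R² of about 1.4% to 2.8% and power of about 85.6% to 86.1%, a gain of one point or less.

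**6. The confounder wording.** No arithmetic applies. Women are randomised at the first antenatal visit (section 6.2.2); complications are recorded after delivery (section 9.5.2). Any that arise in between follow allocation. Section 2.1 lists pyelonephritis and hypertensive disease among the consequences of untreated bacteriuria, so they may be mediators. Set beside this, sections 1.2 and 9.1 give the wrong reason for measuring them.

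**The case against.** The strongest reply is that nothing planned here is invalid. Under simple randomisation the type I error and standard error of the unadjusted test already allow for chance imbalance. That stands: a reader might infer that the primary result will be biased by uneven gestation, and the protocol does not support it. The loss is one of efficiency.

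The size is also uncertain. The protocol gives no figure linking entry gestation to outcome, and the composite includes low birth weight, to which section 9.2 gives the larger rate (14.6% v 10.6%) and which late entry does not close off as it does preterm birth. It would therefore be too strong to say that gestation at entry largely determines the outcome. Setting the 1.3-point shift beside 6.9% × 25% = 1.7 points, the low end of the contribution that section 9.2 attributes to bacteriuria, makes it look alarming. But the shift rests on two assumed inputs and an uncommon imbalance, and adjustment would not rescue a trial with so small an effect: even at 25% v 21.25%, power rises only from about 10% to about 11% at R² = 0.20.

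A reader might also infer that the protocol will adjust for complications. It will not: section 9.2 only describes them as frequencies. Nor does section 9.6 say that no estimate will be reported; the choice of effect measure and interval is commonly left to an analysis plan, which is not shown here.

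None of this defends the confounder wording. And because section 9.6 fixes a single unadjusted test, choosing gestational age as a covariate now is better than choosing it after the data are seen.

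**Conclusion.** The point holds as an improvement to the primary analysis and a correction to the secondary objective and hypothesis, not as a claim of bias. Adjustment for gestational age at entry would raise power from 85.1% to about 85.5–86.9% for an assumed R² of 0.01–0.05, and to 88.6% at 0.10, given 114 evaluable per arm and the planned 25% v 10%. It would also deal with chance imbalance in a way fixed in advance. The gain is modest and rests on an R² that the protocol does not give.

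The confounder wording is wrong whatever those numbers are. Events arising after randomisation cannot confound the comparison of arms, and several may carry part of the effect. Its harm is potential, because no adjustment for them is now planned.

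**What to change.** In section 9.6, prespecify as the primary result the risk difference, with the risk ratio, and 95% confidence intervals, adjusted for gestational age at entry. Standardisation from a logistic model is one way to obtain both. State how gestational age enters (weeks or trimester). Age and number of previous pregnancies may be added, as recorded in Appendix 3; that form has no parity field, so parity should not be named as a covariate. Keep the Pearson chi-square as the unadjusted supporting test. If an analysis plan already specifies this, bring section 9.6 into line with it.

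In sections 1.2 and 9.1, reword the secondary objective and hypothesis as a comparison of maternal and perinatal complications between arms, and state that no event after randomisation enters the primary model.

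The cost is a protocol amendment, best made before outcome data by arm are seen, and slightly more analysis work. No new data and no change to the sample size are needed.

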**10. DATA COLLECTION AND QUALITY ASSURANCE**

**10.1 Data Collection Forms**

The research staff enrolling the participants in antenatal clinic will include an MD doctor and a lab technician. The identification details, inclusion/exclusion criteria, clinical history and examination details of signs and symptoms, and antenatal history will be recorded in a prespecified format by the doctor. The result of the rapid test will be entered by the Principal Investigator in the same format in the designated space.

The outcome assessors will be provided a separate format to record the outcomes. They will be provided only the identification details.

**10.2 Data Management**

Data management will be done by the Principal Investigator. The data collection forms are attached in the Appendix 3 and 4.

**10.3 Quality Assurance**

**10.3.1 Training**

The labor room staff at Gandhi Hospital will be trained for obstetric examination, weight measurement and estimation of gestational age once before the study.

The outcome assessors will be trained for interviewing the client and using the data collection format.

**10.3.2 Quality Control Committee**

NA

**10.3.3 Metrics**

NA

**10.3.4 Protocol Deviations**

Protocol deviation can occur in case any participant is not evaluated properly, or urine sample is not collected as per the guideline. All such incidences will be reported on the data collection format and will be reviewed by the Principal Investigator.

**10.3.5 Monitoring**

Once a week monitoring visit will be made by the Principal Investigator to antenatal clinic. The records and consent forms will be reviewed daily by the Principal Investigator. A sub-sample of 5% of delivered women will be revisited by the Principal Investigator at their home for outcome assessment.

**11. PARTICIPANT RIGHTS AND CONFIDENTIALITY**

**11.1 Institutional Review Board (IRB) Review**

This protocol and the informed consent document (Appendix 1) and any subsequent modifications will be reviewed and approved by the IRB or ethics committee responsible for oversight of the study. An IRB approval will be obtained by submitting proposal, formats, and this protocol.

**11.2 Informed Consent Forms**

A signed consent form will be obtained from each participant. In case a participant is unable to sign, thumb impression will be taken on the informed consent form after undergoing the consent procedure. In case a participant cannot consent herself, a legal guardian will be involved in consent procedure and the same will be documented.

**11.3 Participant Confidentiality**

The data of the participant will be anonymized by safe harbour procedure. All records will be kept in a secured cabinet and all computer entries will be password-protected. The participants will be assigned a serial number for identification.

**11.4 Study Discontinuation**

The study may be discontinued at any time by the IRB, the regulatory bodies, the sponsor, or other government agencies as part of their duties to ensure that research participants are protected.

**12. COMMITTEES**

NA

**13. PUBLICATION OF RESEARCH FINDINGS**

Any presentation, abstract, or manuscript will be made available for review by the sponsor prior to submission.

**15. SUPPLEMENTS/APPENDICES**

**Appendix 3 Data Collection Format for Study Enrollment and Record of Laboratory Reports**

| **RECORD OF ENROLLED MOTHERS** | | | | |
| --- | --- | --- | --- | --- |
| **DATE OF EVALUATION-** | |  | **OPD REGISTRATION NUMBER-** | |
| **ANC NUMBER-** | |  | **LAB NUMBER-** | |
|  | |  |  | |
| **A. Identification Data** | |  | **D. Enrolment details** | |
| **Name-** | |  | **Arm** **of** **the** **study** **for** **which** **woman** **is** **enrolled** | ❑ **Asymptomatic** |
| **Husband’s** **name-** | |  |  | ❑ **Symptomatic** |
| **Address-** | |  | **ENROLMENT NUMBER-** | |
|  |  |  |  | |
| **Mobile/phone** **number-** | |  | **E. Demographic and socioeconomic profile** | |
| **Alternate** **number** **if** **available-** | |  | **Age-** | |
|  | |  | **Religion-** | |
| **B. Exclusion Criteria** | |  | **Education-** | |
| **Has** **pregnant** **woman** **received** **any** **antibiotics** **in** **last** **two** **weeks?** | ❑ **Yes** |  |  | |
|  | ❑ **No** |  | **F. Antenatal data** | |
|  | |  | **No** **of** **previous** **ANC** **visits-** | |
| **Is** **woman** **pregnant** **for** **more** **than** **38** **weeks?** | ❑ **Yes** |  | **Gestational** **age** **in** **weeks-** | |
|  | ❑ **No** |  | **Number** **of** **previous** **pregnancies-** | |
|  | |  | **Number** **of** **abortions-** | |
| **Was** **she** **tested** **for** **Rapid** **Strip** **test** **in** **any** **arm** **of** **study** **earlier?** | ❑ **Yes** |  | **Number** **of** **live** **children-** | |
|  | ❑ **No** |  |  | |
|  | |  | **Was** **she** **tested** **or** **treated** **for** **UTI** **earlier** **in** **this** **pregnancy?** | ❑ **Yes** |
|  | |  |  | ❑ **No** |
| ***Enrolled in the study?*** | ❑ **Yes** |  |  | |
|  | ❑ **No** |  | **G. Study Seal** | |
|  | |  |  | |
| **C. Symptoms- (Tick whichever are applicable-one or**  **more)** | |  |  |  |
| ***Cystitis*** | |  |  |  |
| **Going** **for** **passing** **urine** **frequently** | ❑ |  |  |  |
| **Feel** **like** **urgently** **passing** **urine** | ❑ |  |  |  |
| **Pain/burning** **sensation** **during** **passing** **urine** | ❑ |  |  |  |
| **Urge** **to** **pass** **urine** **at** **night** | ❑ |  |  |  |
| **Lower** **abdominal** **pain** | ❑ |  |  |  |
| **Low-back** **pain** | ❑ |  |  |  |
| **Bleeding** **in** **urine** | ❑ |  |  |  |
| ***Pyelonephritis*** | |  |  |  |
| **Pain** **on** **the** **side** **of** **the** **abdomen** | ❑ |  |  |  |
| **Nausea** | ❑ |  |  |  |
| **Vomiting** | ❑ |  | **H. Outcome of pregnancy** | |
| **Fever** **(>38ºC)** | ❑ |  | **Birth Weight-** | |
| **Costo-vertebral** **angle** **tenderness** | ❑ |  | **Gestational age at delivery-** | |
| **Chills** | ❑ |  | **Any complication/death-** |  |
| ***Asymptomatic*** | |  |  |  |
| **No** **symptoms** | ❑ |  |  |  |

**Appendix 4 Data Collection Format for Outcome Assessors**

Field Data Collection Checklist

| Date of visit |  |
| --- | --- |
| Enrolment number |  |
| ANC Number |  |
| IPD Number |  |
| Name |  |
| Alias/AKA |  |
| Age |  |
| Husband’s Name |  |
| Education |  |
| Did you sign any telugu form at Gandhi Hospital before pregnancy | □Yes □No  □I Don’t remember |
| Date of Delivery |  |
| Name and address of the hospital where she delivered |  |
| Gender of the baby |  |
| Weight of the baby at birth |  |
| Other outcomes/complications/ death during pregnancy/delivery/ postpartum(baby/mother) |  |
| Documents whose pic is collected | □Discharge card □Indoor ticket □Delivery Note □Baby note  □Other-Specify-______________ |
| Signature of Mother |  |

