**3. STUDY DESIGN**

The study will be a parallel-group superiority pragmatic randomized controlled trial with 1:1 allocation, to identify the superiority of the intervention of using a rapid test for informing clinical decision for prescribing antibiotics based on positive AST results, over the usual care in the study hospital in case of asymptomatic bacteriuria in pregnancy. Blinding will be done for outcome assessors.

The only difference between the intervention and control arm will be the information provided by the rapid test regarding the identification of bacteria and susceptibility of antibiotics.

The primary outcome of the study is incidence of preterm birth or low birth weight or both as the outcome of pregnancy. The secondary outcome is incidence of any other maternal or perinatal complication in the study participants.

The study population will be pregnant women attending antenatal clinic of the hospital for first antenatal check-up. The study will have two arms- intervention arm and control arm. In each arm, 120 participants will be enrolled.

The setting of conduct of study will be antenatal outpatient clinic and microbiology laboratory of Gandhi Medical College and Hospital, Secunderabad. The reader machine for the novel test will be installed in the microbiology laboratory of Gandhi Hospital by Department of Biological Sciences, Birla Institute of Technology and Science (BITS) Pilani, Hyderabad Campus. The strips for conducting the test will be provided by Genomics Laboratory, Department of Biological Sciences, BITS Pilani, Hyderabad Campus.

Anticipated duration of study is one year, including a variable follow up period depending upon the Expected Date of Delivery of pregnant women.

Unit of randomization will be pregnant woman. A suitable method of randomization will be adopted out of coin toss, lottery, toss of dice, shuffling cards, MS Excel etc. The randomization sequence will be concealed from the staff enrolling and assessing. Simple randomization method will be adopted to randomly assign participants to either intervention or control group without any restriction. The Principal Investigator will discard urine samples of participants of control arm and will provide urine sample of participants of intervention arm to the staff in laboratory conducting rapid test, as per the randomization sequence. The positive samples will be informed to obstetrician on duty and will be prescribed antibiotics as per the report of the rapid test.

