**4.1 Inclusion Criteria**

The participants must meet all of the inclusion criteria listed below to participate in this study-

1. Confirmed pregnancy based on urine pregnancy test or ultrasonography.

2. Pregnant woman irrespective of the age at the time of enrolment

3. Asymptomatic participant

4. Consenting and willing to provide a written informed consent.

5. Ability to understand study procedures and to comply with them for the entire length of the study

6. Any gravida or parity of woman

7. Pregnant woman coming in any trimester for first antenatal checkup as sometimes they come late during second or third trimester also.

8. History of antibiotic consumption more than one week ago

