**Randomization**

Randomization will be done on the same day of screening, baseline, and urine sample collection. Randomization will be done as soon as the sample reaches microbiology laboratory. The allocation sequence like the one generated by MS excel random number generation feature will be concealed from the research staff who will enroll the participants.

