**6.2.4 Followup Visits**

Although study will not require any additional follow up visit to the hospital, but the participants will be encouraged to come for regular antenatal checkups as scheduled by the obstetricians. The routine tests and assessment of antenatal checkups will be carried out as per the guidelines of the institute. In case of any adverse event or urinary tract infection, the participants will be shared contact number of the Principal Investigator and research staff, who will facilitate the care provision at the hospital.

Since the participants need not deliver in Gandhi Hospital itself, or may not necessarily deliver around the Expected Date of Delivery, a follow up visit will be conducted by outcome assessors to the hospital where they will be admit or at home if the delivery is already over. The coordination will be done around EDD on telephone.

The follow up visit should be completed by the outcome assessors around the delivery or as soon as possible. The outcome assessors will collect data on week of gestation at the time of delivery, birth weight, any maternal or perinatal co-morbidity encountered, and will collect the snapshot of the discharge card or treatment record as per the availability with the participant.

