**Treatment Assignment Procedures**

Randomization allocation sequence will be concealed from the participant enrollment team and will be maintained in the soft copy by the Principal Investigator, who will implement the randomization in a separate room in microbiology laboratory, and will discard the urine samples of the control arm.

No previous records will be shared with the blinded outcome assessors, who will be provided blank printed formats with only the identification details of the participants. No one will be authorized to break the blinding.

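### The secondary outcome is called incidence, but neither data form separates maternal conditions present at randomisation from those arising afterwards

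*Protocol*

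**What the plan says.** **Outcome.** Section 3 states: "The secondary outcome is incidence of any other maternal or perinatal complication in the study participants". Section 9.5.2 states: "Secondary outcome is incidence of other maternal and perinatal morbidities and it will be measured during the same visit as the primary outcome". Neither section lists conditions or says when the at-risk period begins.

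**Entry and randomisation.** Section 4.1 admits a "Pregnant woman coming in any trimester for first antenatal checkup as sometimes they come late during second or third trimester also". Section 6.2.2 adds: "Randomization will be done on the same day of screening, baseline, and urine sample collection". Appendix 3 asks only whether gestation exceeds 38 weeks, so late entry is foreseen.

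**Outcome form.** Appendix 4 has a single free-text entry: "Other outcomes/complications/ death during pregnancy/delivery/ postpartum(baby/mother". The only dates on that form are those of the visit and of delivery. Under section 6.2.4 assessors record "any maternal or perinatal co-morbidity encountered, and will collect the snapshot of the discharge card or treatment record as per the availability".

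**Baseline form.** Appendix 3 records UTI symptoms, earlier UTI testing or treatment in this pregnancy, gestational age and obstetric counts. It has no place for other existing maternal conditions.

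**Use of the data.** Section 9.2 plans to describe these events as frequencies. Sections 1.2 and 9.1 also want them in order to look for confounders of preterm birth and low birth weight.

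**The concern.** An incidence outcome in a randomised trial should count events that begin after randomisation. For maternal antenatal conditions, the form captures whether the condition was present at any time in this pregnancy. For a woman who first attends in the second or third trimester, much of that period lies before randomisation.

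The problem concerns conditions that the protocol itself considers relevant. Section 2.1 names hypertensive disease and anaemia among the consequences of untreated bacteriuria, and either can already exist at a late first visit.

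Two things are at stake. The reported frequencies may be too high for something labelled incidence. The stated confounder purpose also fails: a confounder must precede the process under study, whereas a complication arising after randomisation may be a result of the allocation. One undated field cannot tell the two apart.

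**Working it through.** **Step 1: look for a place where prior and new conditions are separated.**

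| Where | What it provides | Does it separate them? |
|---|---|---|
| Sections 3 and 9.5.2 | The word incidence | No start of the risk period |
| Section 6.2.4 | Any co-morbidity met with | No limit to onset after entry |
| Appendix 4 | One free-text field, no onset date | No |
| Treatment Assignment Procedures (9.2) | "No previous records will be shared with the blinded outcome assessors" | Assessors cannot do it at the visit |
| Section 6.1 | Medical history, vital signs, haematology and blood chemistry at Visit 1 | Possible source, but Appendix 3 has no field for existing conditions |
| Section 9.5 | Principal Investigator validates outcomes from collected records | No onset rule given |

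No entry completes the separation.

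**Step 2: which events are exposed.** Delivery, postpartum and perinatal events necessarily follow randomisation. Preterm birth and low birth weight do too. Only maternal antenatal conditions can predate entry.

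**Step 3: direction and size.** The protocol gives no rate for the secondary outcome, so there is no figure to reproduce. The 120 per arm in section 9.2 concerns the primary outcome and does not bear on this point.

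Assume that each woman is counted once if any maternal antenatal condition is recorded. Let *b* be the share with a prior condition that is counted, equal in both arms as randomisation gives in expectation. Let *r* be the true post-randomisation risk in the remaining women. Then:

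- observed frequency = b + (1 − b) × r
- observed difference between arms = (1 − b) × (true difference)

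With purely illustrative risks of 20% and 10%:

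| b | Higher arm | Lower arm | Difference | Ratio |
|---|---|---|---|---|
| 0% | 20% | 10% | 10 points | 0.50 |
| 10% | 0.10 + 0.90 × 0.20 = 28% | 0.10 + 0.90 × 0.10 = 19% | 9 points | 0.68 |
| 20% | 0.20 + 0.80 × 0.20 = 36% | 0.20 + 0.80 × 0.10 = 28% | 8 points | 0.78 |
| 30% | 0.30 + 0.70 × 0.20 = 44% | 0.30 + 0.70 × 0.10 = 37% | 7 points | 0.84 |

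Frequencies rise in both arms and the contrast shrinks towards no difference. The values of *b* and *r* are not in the protocol. The table shows the mechanism and does not forecast this trial.

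**The case against.** **The wording leans towards new events.** Incidence, and complications occurring in enrolled women (section 1.2), both suggest events after entry. A reader might infer from Appendix 4 that the protocol counts prior conditions as outcomes. No section says so, and none excludes them. The documents support only that such conditions can be counted.

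**No comparison is planned.** Section 9.2 promises descriptive frequencies, and the chi-square test in section 9.6 is for preterm birth or low birth weight. A reader might infer that a secondary treatment effect will be estimated with bias. No secondary test or effect estimate is stated, so dilution touches only an informal reading by arm. This objection stands and limits the importance of the point.

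**Records could date some conditions.** Visit 1 history and laboratory tests, and the hospital documents photographed later, may show when a condition began. This stands in part. No section says they will be used this way, and the hospital documents are collected only where the participant has them. The Principal Investigator, who would do the sorting, also holds the allocation sequence and enters the rapid test results (Treatment Assignment Procedures; section 10.1). Retrospective judgement would therefore be unblinded.

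**The analysis plan can set the window.** It can, but it cannot reliably recover onset dates that the forms never asked for. The missing fields are a matter for this document.

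**Any specific dilution figure is speculative.** Agreed. The protocol gives no distribution of gestation at entry, no complication rates and no expected effect on them. With bacteriuria in 1.9 to 9.5% of women (section 2.1), a large effect on complications across all women would itself be surprising. If women with and without bacteriuria had equal risk, abolishing every complication in the former would give a risk ratio of about 1 − 0.095 = 0.905 at most favourable.

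**Conclusion.** The point holds in a limited form. For maternal antenatal conditions, the forms measure presence at any time in the pregnancy while the outcome is named incidence, and nothing in the protocol separates prior from new conditions. The descriptive frequencies can be too high, an informal contrast between arms would be diluted by the factor 1 − b, and the data cannot serve the confounder purpose as collected.

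It does not follow that either arm is favoured, since prior conditions are balanced in expectation. Nor does it follow that the primary outcome, the sample size or the events at and after delivery are affected. The size cannot be derived from the documents. The illustration rests on assumed rates, equal prior shares in the arms and counting per woman. The forms should be corrected, but the flaw does not threaten the trial's main conclusion.

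**What to change.** 1. **Appendix 4:** add, for each complication, the date or gestational week at which it was first diagnosed. Appendix 3 already has the date of evaluation and gestational age at entry, so the comparison is then mechanical and needs no unblinded judgement.
2. **Appendix 3:** add a field for existing maternal conditions, filled from the history, vital signs and haematology already scheduled at Visit 1.
3. **Section 9.5.2:** state that a maternal condition counts as a secondary outcome only if it was absent at the enrolment visit and first diagnosed after randomisation. Tabulate prior conditions by arm as baseline characteristics. These, rather than later complications, are the candidates for the confounder question in sections 1.2 and 9.1.

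The cost is two form fields and a short rule, with no extra visit and no change to the sample size. Slightly fewer events will be counted and some dates will be missing. Because enrolment is the first antenatal visit and diagnosis is not onset, a condition present but undiagnosed at entry may still be counted, and the report should say so.
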